**NONE**

**0**

**ALL**

**10**

**
[figure not shown]
**

*_____-1. Don’t know*

*_____-2. Refused*

G7. When was the last time you missed any of your medications?

_____ 5. Within the past week

_____ 4. 1-2 weeks ago

_____ 3. 2-4 weeks ago

_____ 2. 1-3 months ago

_____ 1. More than 3 months ago

_____ 0. Never skip medications *Skip to H1 in next section*

*_____-1. Don’t know*

*_____-2. Refused*

G8. Some people find that they may go without pills for more than 2 days at a time. In the last 6 months, have you ever not taken or missed your medications for more than 2 days at a time?

_____ 0. No  Go to H1

_____ 1. Yes

*_____-1. Don’t know*

*_____-2. Refused*

G9. Here is a list of possible reasons why you may miss taking your medications for more than 2 days at a time. In the last 6 months, have you missed taking your HIV medications for more than 2 days at a time because you:

|  | **No** | **Yes** | *Don’t know* | *Refused* |
| --- | --- | --- | --- | --- |
| 1. Were away from home? | 0 | 1 | *-1* | *-2* |
| 1. Were busy with other things? | 0 | 1 | *-1* | *-2* |
| 1. Simply forgot? | 0 | 1 | *-1* | *-2* |
| 1. Had too many pills to take? | 0 | 1 | *-1* | *-2* |
| 1. Wanted to avoid side effects? | 0 | 1 | *-1* | *-2* |
| 1. Did not want others to notice you taking medication? | 0 | 1 | *-1* | *-2* |
| 1. Had a change in daily routine? | 0 | 1 | *-1* | *-2* |
| 1. Felt like the drug was toxic/harmful? | 0 | 1 | *-1* | *-2* |
| 1. Fell asleep/slept through dose time? | 0 | 1 | *-1* | *-2* |
| 1. Felt sick or ill? | 0 | 1 | *-1* | *-2* |
| 1. Felt depressed /overwhelmed? | 0 | 1 | *-1* | *-2* |
| 1. Had problems with taking pills at specified times (with meals, on empty stomach, etc.)? | 0 | 1 | *-1* | *-2* |
| 1. Ran out of pills? | 0 | 1 | *-1* | *-2* |
| 1. Felt good? | 0 | 1 | *-1* | *-2* |
| 1. Did not have enough food to take with pills? | 0 | 1 | *-1* | *-2* |
| 1. Could not get transportation to the clinic to pick up more pills? | 0 | 1 | *-1* | *-2* |

*[After completing G9, go to H1 in next section.]*

**Only for Participants NOT taking HIV Medications**

G10.

| ***Interviewer Reads:*** “The following are some reasons other people have told us why they are **not** currently taking any HIV medications. After I read you each reason, please tell me if it describes you.” |
| --- |

|  | **No** | **Yes** | *Don’t know* | *Refused* |
| --- | --- | --- | --- | --- |
| 1. No doctor or other medical provider has ever offered HIV medications to me. | 0 | 1 | *-1* | *-2* |
| 1. A medical provider offered them to me, but I choose not to take HIV medications at this time. | 0 | 1 | *-1* | *-2* |
| 1. I discussed taking HIV medications with my medical provider, but he/she did not think it was a good idea for me now. | 0 | 1 | *-1* | *-2* |
| 1. My CD4 (T-cell) count is too high for me to take HIV medications. | 0 | 1 | *-1* | *-2* |
| 1. I tried HIV medications, but there were too many unpleasant side effects. | 0 | 1 | *-1* | *-2* |
| 1. I tried HIV medications, but they were not effective for me. | 0 | 1 | *-1* | *-2* |
| 1. I tried HIV medications, but they were too difficult to take as prescribed. | 0 | 1 | *-1* | *-2* |
| 1. I cannot afford them. | 0 | 1 | *-1* | *-2* |
| 1. Is there any other reason why you are not currently taking any HIV medications?   ***If yes*:** Reason __________________________ | 0 | 1 | *-1* | *-2* |

**Disclosure**

| ***Interviewer Reads:*** “Now, I am going to ask you some questions about people you have told that you are HIV-positive.” |
| --- |

H1. Have you ever told anyone that you are HIV positive?

_____ 0. No *Skip to H5*

_____ 1. Yes

*_____-1. Don’t know*

*_____-2. Refused*

H2. How many people have you told?

__________ Number told

*_____-1. Don’t know*

*_____-2. Refused*

H3. How many household members have you told?

__________ Number told

*_____-1. Don’t know*

*_____-2. Refused*

H4. Have you ever disclosed your HIV status to any of the following people?

|  | **No** | **Yes** | *Don’t know* | *Refused* |
| --- | --- | --- | --- | --- |
| a. Any parent? | 0 | 1 | *-1* | *-2* |
| b. Any biological child? | 0 | 1 | *-1* | *-2* |
| c. Any relative? | 0 | 1 | *-1* | *-2* |
| d. Any friend? | 0 | 1 | *-1* | *-2* |
| e. Any spouse? | 0 | 1 | *-1* | *-2* |
| f. Any sex partner? | 0 | 1 | *-1* | *-2* |

H5. Are you worried about other people finding out your HIV status?

_____ 0. No

_____ 1. Yes

*_____-1. Don’t know*

*_____-2. Refused*

H6. What do you think might happen if people that you have not told found out your HIV status?  *[Do not read responses. Tick all that apply.]*

_____ 1. Might be fired/lose a job/denied a job

_____ 2**.** Family members might treat you differently/not respect your opinion

_____ 3. Might lose friends

_____ 4. Partner might get violent

_____ 5. People might start gossiping about you

_____ 6. Might be kicked out of your home/ become homeless

_____ 7. In-laws might encourage spouse to leave you

_____ 8. Your children might be abused or discriminated against

_____ 9. Your children might become upset/fearful

_____ 10. Might not get good care/hospital/home/school etc.

_____ 11. Might cause the other person’s health to deteriorate or other

person to become anxious

_____ 12. Nothing

_____ 13. Other (Specify):__________________

*_____-1. Don’t know*

*_____-2. Refused*

**HIV/AIDS** **Knowledge**

| ***Interviewer reads:*** “Now I would like to ask you some questions about HIV and AIDS.” |
| --- |

H101. If a man has the virus that causes AIDS, does his sexual partner always have the AIDS virus, almost always, or only sometimes?

_____ 1. Always

_____ 2. Almost always

_____ 3. Only sometimes

*_____-1. Don’t know*

*_____-2. Refused*

H102. If a woman has the virus that causes AIDS, does her sexual partner always have the AIDS virus, almost always, or only sometimes?

_____ 1. Always

_____ 2. Almost always

_____ 3. Only sometimes

*_____-1. Don’t know*

*_____-2. Refused*

H103. What are the main channels of communication from which you receive AIDS information and education? Probe: Any other channels*?* *[Don’t read responses. Record ALL channels mentioned.]*

_____ 1. Radio

_____ 2. Television

_____ 3. Film

_____ 4. Drama

_____ 5. Newspapers/magazines

_____ 6. Brochures

_____ 7. Posters

_____ 8. Billboards

_____ 9. Community notices

_____ 10. Family

_____ 11. Friends

_____ 12. Peers

_____ 13. Health workers

_____ 14. Teachers

_____ 15. Political leaders

_____ 16. Traditional leaders

_____ 17. Religious leaders

_____ 18. Internet

_____ 19. Other people living with HIV/AIDS

_____ 20. Other (specify) _____________________

*_____-1. Don’t know*

*_____-2. Refused*

**Patient Sex Behavior**

| ***Interviewer reads:*  “**Now I would like to ask you some questions about your recent sexual activity. We know these questions are sensitive and want to remind you that your answers are completely private and will not be shared with anyone. No one will know what particular answers you give. It is perfectly normal for persons with HIV to have sex. We are not judging you on your sexual behaviors. We want you to be as honest as you can answering these questions. If we should come to any questions that you don’t want to answer, just let me know and we will go to the next one.  Different people have different definitions of ‘sex’ or ‘sexual intercourse.’ For this study, sex can include several things, such as:   - Vaginal sex, which is when a man puts his penis in a woman’s vagina. - Anal sex, which is when a man puts his penis in another person’s rectum or butt.” |
| --- |

J1. How old were you when you had sexual intercourse for the very first time?

__________Age in years

*_____-1. Don’t know*

*_____-2. Refused*

J2. In total, how many different people have you had sexual intercourse with in your entire life?

__________Total number of lifetime partners

*_____-1. Don’t know*

*_____-2. Refused*

J3. Have you had sexual intercourse in the last 3 months?

_____ 0. No  *Skip to K1 in next section.*

_____ 1. Yes

*_____-1. Don’t know*

*_____-2. Refused*

J4. In total, how many people have you had sex with in the last 3 months?

__________ Total number of partners

*_____-1. Don’t know*

*_____-2. Refused*

J5. In total, how many people have you had sex with in the last 2 weeks?

__________ Total number of partners

*_____-1. Don’t know*

*_____-2. Refused*

| ***Interviewer reads:*** “I am going to ask you about the people you had sex with over the past 90 days. Please tell me about them starting with your most recent sexual partner.” |
| --- |

*[****Interviewer:*** *Read down each column of the table (for each partner, one at a time),* ***not*** *across each row.]*

|  | **Partner 1** | **Partner 2** | **Partner 3** | **Partner 4** | **Partner 5** |
| --- | --- | --- | --- | --- | --- |
| J6. What is the first name or a nickname of this partner? | ___ *-1. Don’t know*  ___ *-2. Refused* | ___ *-1. Don’t know*  ___ *-2. Refused* | ___ *-1. Don’t know*  ___ *-2. Refused* | ___ *-1. Don’t know*  ___ *-2. Refused* | ___ *-1. Don’t know*  ___ *-2. Refused* |
| For the next question I am going to ask you if a partner is a **spouse**, **main partner**, or **non-main partner**.   - By **spouse** we mean someone who you are married to or living with as if married. - By **main partner** we mean someone who you are NOT married to or living with as if married, but who is a steady partner such as a boyfriend or girlfriend. - By **non-main partner** we mean someone who is NOT your spouse or a main partner, but with whom you have had sex with in the last 3 months. | | | | | |
| J7. Is this person your spouse, main partner, or non-main partner? | ___ 1. Spouse  ___ 2. Main  ___ 3. Non-main  ___ *-1. Don’t know*  ___ *-2. Refused* | ___ 1. Spouse  ___ 2. Main  ___ 3. Non-main  ___ *-1. Don’t know*  ___ *-2. Refused* | ___ 1. Spouse  ___ 2. Main  ___ 3. Non-main  ___ *-1. Don’t know*  ___ *-2. Refused* | ___ 1. Spouse  ___ 2. Main  ___ 3. Non-main  ___ *-1. Don’t know*  ___ *-2. Refused* | ___ 1. Spouse  ___ 2. Main  ___ 3. Non-main  ___ *-1. Don’t know*  ___ *-2. Refused* |
| J8. When was the first time you had sex with this partner? | ________ Days ago  ________ Weeks ago  ________ Months ago  ________ Years ago  ___ *-1. Don’t know*  ___ *-2. Refused* | ________ Days ago  ________ Weeks ago  ________ Months ago  ________ Years ago  ___ *-1. Don’t know*  ___ *-2. Refused* | ________ Days ago  ________ Weeks ago  ________ Months ago  ________ Years ago  ___ *-1. Don’t know*  ___ *-2. Refused* | ________ Days ago  ________ Weeks ago  ________ Months ago  ________ Years ago  ___ *-1. Don’t know*  ___ *-2. Refused* | ________ Days ago  ________ Weeks ago  ________ Months ago  ________ Years ago  ___ *-1. Don’t know*  ___ *-2. Refused* |
| J9. When was the last time you had sex with this partner? | ________ Days ago  ________ Weeks ago  ________ Months ago  ___ *-1. Don’t know*  ___ *-2. Refused* | ________ Days ago  ________ Weeks ago  ________ Months ago  ___ *-1. Don’t know*  ___ *-2. Refused* | ________ Days ago  ________ Weeks ago  ________ Months ago  ___ *-1. Don’t know*  ___ *-2. Refused* | ________ Days ago  ________ Weeks ago  ________ Months ago  ___ *-1. Don’t know*  ___ *-2. Refused* | ________ Days ago  ________ Weeks ago  ________ Months ago  ___ *-1. Don’t know*  ___ *-2. Refused* |
| J10. Are you still in a sexual relationship with this partner? | ___ 0. No  ___ 1. Yes  ___ *-1. Don’t know*  ___ *-2. Refused* | ___ 0. No  ___ 1. Yes  ___ *-1. Don’t know*  ___ *-2. Refused* | ___ 0. No  ___ 1. Yes  ___ *-1. Don’t know*  ___ *-2. Refused* | ___ 0. No  ___ 1. Yes  ___ *-1. Don’t know*  ___ *-2. Refused* | ___ 0. No  ___ 1. Yes  ___ *-1. Don’t know*  ___ *-2. Refused* |
| J11. Since you first had sex with this partner, how many other people have you had sex with during the sexual relationship? | _______ [# of partners]  ___ *-1. Don’t know*  ___ *-2. Refused* | _______ [# of partners]  ___ *-1. Don’t know*  ___ *-2. Refused* | _______ [# of partners]  ___ *-1. Don’t know*  ___ *-2. Refused* | _______ [# of partners]  ___ *-1. Don’t know*  ___ *-2. Refused* | _______ [# of partners]  ___ *-1. Don’t know*  ___ *-2. Refused* |
| J12. Has this partner been tested for HIV? | ___ 0. No** J16**  ___ 1. Yes  __*-1.Don’t know***J16**  __ *-2. Refused*** J16** | ___ 0. No** J16**  ___ 1. Yes  __*-1.Don’t know***J16**  __ *-2. Refused*** J16** | ___ 0. No** J16**  ___ 1. Yes  __*-1.Don’t know***J16**  __ *-2. Refused*** J16** | ___ 0. No** J16**  ___ 1. Yes  __*-1.Don’t know***J16**  __ *-2. Refused*** J16** | ___ 0. No** J16**  ___ 1. Yes  __*-1.Don’t know***J16**  __ *-2. Refused*** J16** |
| J13. How long ago was this partner tested for HIV? | ____ Days ago  ____ Months ago  ____ Years ago  ___ *-1. Don’t know*  ___ *-2. Refused* | ____ Days ago  ____ Months ago  ____ Years ago  ___ *-1. Don’t know*  ___ *-2. Refused* | ____ Days ago  ____ Months ago  ____ Years ago  ___ *-1. Don’t know*  ___ *-2. Refused* | ____ Days ago  ____ Months ago  ____ Years ago  ___ *-1. Don’t know*  ___ *-2. Refused* | ____ Days ago  ____ Months ago  ____ Years ago  ___ *-1. Don’t know*  ___ *-2. Refused* |
| J14. Do you know this partner’s HIV status? | ___ 0. No** J16**  ___ 1. Yes  __*-1.Don’t know***J16**  __ *-2. Refused*** J16** | ___ 0. No** J16**  ___ 1. Yes  __*-1.Don’t know***J16**  __ *-2. Refused*** J16** | ___ 0. No** J16**  ___ 1. Yes  __*-1.Don’t know***J16**  __ *-2. Refused*** J16** | ___ 0. No** J16**  ___ 1. Yes  __*-1.Don’t know***J16**  __ *-2. Refused*** J16** | ___ 0. No** J16**  ___ 1. Yes  __*-1.Don’t know***J16**  __ *-2. Refused*** J16** |
| J15. What is this partner’s HIV status? | ___ 0. HIV-Positive** J18**  ___ 1. HIV-Negative  ___ *-1. Don’t know*  ___ *-2. Refused* | ___ 0. HIV-Positive** J18**  ___ 1. HIV-Negative  ___ *-1. Don’t know*  ___ *-2. Refused* | ___ 0. HIV-Positive** J18**  ___ 1. HIV-Negative  ___ *-1. Don’t know*  ___ *-2. Refused* | ___ 0. HIV-Positive** J18**  ___ 1. HIV-Negative  ___ *-1. Don’t know*  ___ *-2. Refused* | ___ 0. HIV-Positive** J18**  ___ 1. HIV-Negative  ___ *-1. Don’t know*  ___ *-2. Refused* |
| J16. How confident are you that you could talk with this partner in the next month about getting tested for HIV? | ___ 1. Very confident  ___ 2. Confident  ___ 3. Somewhat  confident  ___ 4. Not at all  confident  ___ *-1. Don’t know*  ___ *-2. Refused* | ___ 1. Very confident  ___ 2. Confident  ___ 3. Somewhat  confident  ___ 4. Not at all  confident  ___ *-1. Don’t know*  ___ *-2. Refused* | ___ 1. Very confident  ___ 2. Confident  ___ 3. Somewhat  confident  ___ 4. Not at all  confident  ___ *-1. Don’t know*  ___ *-2. Refused* | ___ 1. Very confident  ___ 2. Confident  ___ 3. Somewhat  confident  ___ 4. Not at all  confident  ___ *-1. Don’t know*  ___ *-2. Refused* | ___ 1. Very confident  ___ 2. Confident  ___ 3. Somewhat  confident  ___ 4. Not at all  confident  ___ *-1. Don’t know*  ___ *-2. Refused* |
| J17. How worried are you about transmitting HIV to this partner? | ___ 1. Very worried  ___ 2. Somewhat  worried  ___ 3. Not at all  worried  ___ *-1. Don’t know*  ___ *-2. Refused* | ___ 1. Very worried  ___ 2. Somewhat  worried  ___ 3. Not at all  worried  ___ *-1. Don’t know*  ___ *-2. Refused* | ___ 1. Very worried  ___ 2. Somewhat  worried  ___ 3. Not at all  worried  ___ *-1. Don’t know*  ___ *-2. Refused* | ___ 1. Very worried  ___ 2. Somewhat  worried  ___ 3. Not at all  worried  ___ *-1. Don’t know*  ___ *-2. Refused* | ___ 1. Very worried  ___ 2. Somewhat  worried  ___ 3. Not at all  worried  ___ *-1. Don’t know*  ___ *-2. Refused* |
| J18. Have you told this partner that you are HIV-positive? | ___ 0. No ** J21**  ___ 1. Yes  __*-1. Don’t know***J22**  __ *-2. Refused* ** J22** | ___ 0. No ** J21**  ___ 1. Yes  __*-1. Don’t know***J22**  __ *-2. Refused* ** J22** | ___ 0. No ** J21**  ___ 1. Yes  __*-1. Don’t know***J22**  __ *-2. Refused* ** J22** | ___ 0. No ** J21**  ___ 1. Yes  __*-1. Don’t know***J22**  __ *-2. Refused* ** J22** | ___ 0. No ** J21**  ___ 1. Yes  __*-1. Don’t know***J22**  __ *-2. Refused* ** J22** |
| J19. How long ago did you tell this partner that you are HIV-positive? | ____ Days ago  ____ Months ago  ____ Yearsago  ___ *-1. Don’t know*  ___ *-2. Refused* | ____ Days ago  ____ Months ago  ____ Years ago  ___ *-1. Don’t know*  ___ *-2. Refused* | ____ Days ago  ____ Months ago  ____ Years ago  ___ *-1. Don’t know*  ___ *-2. Refused* | ____ Days ago  ____ Months ago  ____ Yearsago  ___ *-1. Don’t know*  ___ *-2. Refused* | ____ Days ago  ____ Months ago  ____ Years ago  ___ *-1. Don’t know*  ___ *-2. Refused* |
| J20. When you told this partner you are HIV-positive did your partner hit, slap, kick, or do anything else to hurt you physically? | ___ 0. No  ___ 1. Yes  ___ *-1. Don’t know*  ___ *-2. Refused*  **Go to J22** | ___ 0. No  ___ 1. Yes  ___ *-1. Don’t know*  ___ *-2. Refused*  **Go to J22** | ___ 0. No  ___ 1. Yes  ___ *-1. Don’t know*  ___ *-2. Refused*  **Go to J22** | ___ 0. No  ___ 1. Yes  ___ *-1. Don’t know*  ___ *-2. Refused*  **Go to J22** | ___ 0. No  ___ 1. Yes  ___ *-1. Don’t know*  ___ *-2. Refused*  **Go to J22** |
| *If ‘no’ to J18:*  J21. How confident are you that you could tell this partner about your HIV status in the next month? | ___ 1. Very confident  ___ 2. Confident  ___ 3. Somewhat confident  ___ 4. Not at all confident  ___ *-1. Don’t know*  ___ *-2. Refused* | ___ 1. Very confident  ___ 2. Confident  ___ 3. Somewhat confident  ___ 4. Not at all confident  ___ *-1. Don’t know*  ___ *-2. Refused* | ___ 1. Very confident  ___ 2. Confident  ___ 3. Somewhat confident  ___ 4. Not at all confident  ___ *-1. Don’t know*  ___ *-2. Refused* | ___ 1. Very confident  ___ 2. Confident  ___ 3. Somewhat confident  ___ 4. Not at all confident  ___ *-1. Don’t know*  ___ *-2. Refused* | ___ 1. Very confident  ___ 2. Confident  ___ 3. Somewhat confident  ___ 4. Not at all confident  ___ *-1. Don’t know*  ___ *-2. Refused* |
| J22. Does this partner provide any financial support to you or any of your children? | ___ 0. No  ___ 1. Yes  ___ *-1. Don’t know*  ___ *-2. Refused* | ___ 0. No  ___ 1. Yes  ___ *-1. Don’t know*  ___ *-2. Refused* | ___ 0. No  ___ 1. Yes  ___ *-1. Don’t know*  ___ *-2. Refused* | ___ 0. No  ___ 1. Yes  ___ *-1. Don’t know*  ___ *-2. Refused* | ___ 0. No  ___ 1. Yes  ___ *-1. Don’t know*  ___ *-2. Refused* |
| J23.Do you provide any financial support to this partner? | ___ 0. No  ___ 1. Yes  ___ *-1. Don’t know*  ___ *-2. Refused* | ___ 0. No  ___ 1. Yes  ___ *-1. Don’t know*  ___ *-2. Refused* | ___ 0. No  ___ 1. Yes  ___ *-1. Don’t know*  ___ *-2. Refused* | ___ 0. No  ___ 1. Yes  ___ *-1. Don’t know*  ___ *-2. Refused* | ___ 0. No  ___ 1. Yes  ___ *-1. Don’t know*  ___ *-2. Refused* |
| J24. In the past 90 days, how many times did you have vaginal sex with this partner? | ________ [# of times]  **If 0, skip to J29**  ___ *-1. Don’t know*  ___ *-2. Refused* | ________ [# of times]  **If 0, skip to J29**  ___ *-1. Don’t know*  ___ *-2. Refused* | ________ [# of times]  **If 0, skip to J29**  ___ *-1. Don’t know*  ___ *-2. Refused* | ________ [# of times]  **If 0, skip to J29**  ___ *-1. Don’t know*  ___ *-2. Refused* | ________ [# of times]  **If 0, skip to J29**  ___ *-1. Don’t know*  ___ *-2. Refused* |
| J25. How many of these times in the past 90 days did you use a condom during vaginal sex? | ________ [# of times]  ___ *-1. Don’t know*  ___ *-2. Refused* | ________ [# of times]  ___ *-1. Don’t know*  ___ *-2. Refused* | ________ [# of times]  ___ *-1. Don’t know*  ___ *-2. Refused* | ________ [# of times]  ___ *-1. Don’t know*  ___ *-2. Refused* | ________ [# of times]  ___ *-1. Don’t know*  ___ *-2. Refused* |
| J26. Did you or your partner use a condom the last time you had vaginal sex together? | ___ 0. No  ___ 1. Yes  ___ *-1. Don’t know*  ___ *-2. Refused* | ___ 0. No  ___ 1. Yes  ___ *-1. Don’t know*  ___ *-2. Refused* | ___ 0. No  ___ 1. Yes  ___ *-1. Don’t know*  ___ *-2. Refused* | ___ 0. No  ___ 1. Yes  ___ *-1. Don’t know*  ___ *-2. Refused* | ___ 0. No  ___ 1. Yes  ___ *-1. Don’t know*  ___ *-2. Refused* |
| J27. During the past 14 days, how many times did you have vaginal sex with this partner? | ________ [# of times]  **If 0, skip to J29**  ___ *-1. Don’t know*  ___ *-2. Refused* | ________ [# of times]  **If 0, skip to J29**  ___ *-1. Don’t know*  ___ *-2. Refused* | ________ [# of times]  **If 0, skip to J29**  ___ *-1. Don’t know*  ___ *-2. Refused* | ________ [# of times]  **If 0, skip to J29**  ___ *-1. Don’t know*  ___ *-2. Refused* | ________ [# of times]  **If 0, skip to J29**  ___ *-1. Don’t know*  ___ *-2. Refused* |
| J28. How many of these times in the past 14 days did you use a condom during vaginal sex? | ________ [# of times]  ___ *-1. Don’t know*  ___ *-2. Refused* | ________ [# of times]  ___ *-1. Don’t know*  ___ *-2. Refused* | ________ [# of times]  ___ *-1. Don’t know*  ___ *-2. Refused* | ________ [# of times]  ___ *-1. Don’t know*  ___ *-2. Refused* | ________ [# of times]  ___ *-1. Don’t know*  ___ *-2. Refused* |
| J29. In the past 90 days, how many times did you have anal sex with this partner? | ________ [# of times]  **If 0, skip to J6**  ___ *-1. Don’t know*  ___ *-2. Refused* | ________ [# of times]  **If 0, skip to J6**  ___ *-1. Don’t know*  ___ *-2. Refused* | ________ [# of times]  **If 0, skip to J6**  ___ *-1. Don’t know*  ___ *-2. Refused* | ________ [# of times]  **If 0, skip to J6**  ___ *-1. Don’t know*  ___ *-2. Refused* | ________ [# of times]  **If 0, skip to K1**  ___ *-1. Don’t know*  ___ *-2. Refused* |
| J30. How many of these times in the past 90 days did you use a condom during anal sex? | ________ [# of times]  ___ *-1. Don’t know*  ___ *-2. Refused* | ________ [# of times]  ___ *-1. Don’t know*  ___ *-2. Refused* | ________ [# of times]  ___ *-1. Don’t know*  ___ *-2. Refused* | ________ [# of times]  ___ *-1. Don’t know*  ___ *-2. Refused* | ________ [# of times]  ___ *-1. Don’t know*  ___ *-2. Refused* |
| J31. Did you or your partner use a condom the last time you had anal sex together? | ___ 0. No  ___ 1. Yes  ___ *-1. Don’t know*  ___ *-2. Refused* | ___ 0. No  ___ 1. Yes  ___ *-1. Don’t know*  ___ *-2. Refused* | ___ 0. No  ___ 1. Yes  ___ *-1. Don’t know*  ___ *-2. Refused* | ___ 0. No  ___ 1. Yes  ___ *-1. Don’t know*  ___ *-2. Refused* | ___ 0. No  ___ 1. Yes  ___ *-1. Don’t know*  ___ *-2. Refused* |
| J32. During the past 14 days, how many times did you have anal sex with this partner? | ________ [# of times]  **If 0, skip to J6**  ___ *-1. Don’t know*  ___ *-2. Refused* | ________ [# of times]  **If 0, skip to J6**  ___ *-1. Don’t know*  ___ *-2. Refused* | ________ [# of times]  **If 0, skip to J6**  ___ *-1. Don’t know*  ___ *-2. Refused* | ________ [# of times]  **If 0, skip to J6**  ___ *-1. Don’t know*  ___ *-2. Refused* | ________ [# of times]  **If 0, skip to K1**  ___ *-1. Don’t know*  ___ *-2. Refused* |
| J33. How many of these times in the past 14 days did you use a condom during anal sex? | ________ [# of times]  ___ *-1. Don’t know*  ___ *-2. Refused* | ________ [# of times]  ___ *-1. Don’t know*  ___ *-2. Refused* | ________ [# of times]  ___ *-1. Don’t know*  ___ *-2. Refused* | ________ [# of times]  ___ *-1. Don’t know*  ___ *-2. Refused* | ________ [# of times]  ___ *-1. Don’t know*  ___ *-2. Refused* |

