***Health Care Provider-delivered Prevention Messages***

*1) 5 HIV Prevention Steps for PLWHA in HIV Care and Treatment Settings*

and

*HIV Prevention Messages for PLWHA in HIV Care and Treatment Settings*

Background: Delivering prevention messages to HIV-positive individuals in care and treatment settings can significantly impact the HIV transmission risk behavior of infected persons. Two US-based health care provider-delivered interventions involving providers discussing prevention topics (e.g., serostatus disclosure, consistent condom use) were found to be effective at decreasing the rate of unprotected sex in HIV-positive individuals (Fisher et al., 2006; Richardson et al., 2004). In addition, these studies showed that integrating brief prevention discussions into routine clinic visits in busy medical settings was feasible. Training health care providers to routinely deliver prevention messages to HIV-positive patients in care and treatment settings in sub-Saharan African countries may also be an effective prevention strategy to facilitate reduction of sexual risk behaviors. The intervention and materials developed for this project were adapted from Partnership for Health (Richardson et al., 2004). The investigators obtained input from health care providers in Kenya, Uganda, and Botswana for the adaptation of the materials for the African context and field tested the interventions in 3 clinics in Kenya. The original intervention was expanded to include additional prevention messages and services to more comprehensively address prevention for HIV positive persons and to meet the demands of the African setting.

Intervention Components:

HIV health care providers (e.g., doctors, clinical officers, nurses) and professional staff (e.g., social workers, pharmacists) who are involved with the care of HIV infected patients in the HIV clinic will assess prevention issues and deliver specific prevention messages during routine clinic visits. Specifically, providers will do the following:

- Assess whether patient is sexually active
- Assess whether sex partner(s) have been tested for HIV and refer partner(s) for testing
- Assess whether patient has disclosed to sex partner(s) and encourage disclosure
- Encourage adoption of safer sex behaviors (e.g., abstain or be faithful to one partner, reduce number of partners, and use condoms with every sexual encounter)
- Explain the negative consequences of having sex without a condom

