Project enrollment will occur over of a 2-3 month period at both intervention and comparison clinics. Following completion of the baseline data collection, the intervention will be implemented at the intervention clinics. Because of the baseline data collection period, the 6-month follow-up will be scheduled for a time estimated to be 6-months after the intervention is integrated into the clinic, so that all intervention clinic participants will have an opportunity to be exposed to the intervention following staff training and implementation. To make the intervention and comparison clinic project procedures as similar as possible, the intervention and comparison clinic 6-month follow-up interviews will occur during the same time period. The same battery of questionnaires will be administered to participants at the 6- and 12-month follow-up interviews, with the exception of some of the sociodemographic questions and items asking about whether something had “ever” happened. At each follow up interview, participants will be offered a soda or other drink and reimbursed for travel costs to the clinic upon completion of the interviews.

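### At follow-up the per-partner HIV-testing and disclosure items are skipped for patients who have stopped having sex, a behaviour the package encourages, so analysing those asked is not a full intent-to-treat comparison.

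*Protocol*

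**What the plan says.** **The outcomes.** The Hypotheses section predicts more partner testing and more disclosure to sex partners in intervention clinics over 12 months. The Variables section lists both among the primary outcome variables and commits to intent-to-treat.

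**The skip.** Item J3 of Appendix H (Patient Sex Behavior) asks "Have you had sexual intercourse in the last 3 months". The instruction beside No is "Skip to K1 in next section", so J4 to J33 are not asked. Don't know and Refused carry no skip. The block opens with "I am going to ask you about the people you had sex with over the past 90 days" and has room for five partners. Inside it are "J12. Has this partner been tested for HIV", with J13-J15 on timing and status, and "J18. Have you told this partner that you are HIV-positive", with J19 on timing.

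**When the skip acts.** Recent sexual activity is an inclusion criterion. The Data collection section uses the same battery at 6 and 12 months, except for some sociodemographic questions and "items asking about whether something had “ever” happened".

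**The intervention.** Providers encourage safer behaviours, for example "abstain or be faithful to one partner, reduce number of partners, and use condoms with every sexual encounter".

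**The concern.** J3 decides who is asked about partner testing and disclosure. At baseline it should exclude almost nobody. At follow-up it excludes patients who have stopped having sex, which is one of the changes the package encourages. If that change is more common in intervention clinics, and is related to whether the partner was tested or told, the patients still asked in the two arms are no longer comparable. A difference could then appear with no extra test or disclosure, or a real one could be hidden.

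The 90-day roster has a related effect among patients who remain active: a partner dropped from the relationship also drops out of the measure.

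This is more than an analysis detail left to a statistical analysis plan, because the questionnaire fixes which answers exist. Multiple imputation, which the Data analysis plan section proposes for repeating the primary outcome analysis, could fill these gaps only under assumptions the data cannot test.

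**Working it through.** The protocol gives no figure on this point. The check has three parts: other sources for the two outcomes, the possible size of the bias, and whether scoring abstinence would remove it.

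**1. Is either outcome measured elsewhere, alike in both arms?**

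| Source | Depends on J3? | What it gives |
|---|---|---|
| H4e, H4f (disclosed to any spouse, any sex partner) | No; asked unless H1 is No | Lifetime wording. It may fall under the follow-up exception, and it does not show disclosure to a current partner |
| Q6b, Q6c (disclosed; partner tested) | No | Changes made after talking with providers, so tied to exposure |
| R8b, R8c (same topics) | No, but only if a counselor was seen | Changes made after talking with a counselor |
| Medical chart review | No | The text promises partner HIV status; the Appendix P form shows no field for it |
| Lay Counselor Record | No | Has a box for partner tested; completed in intervention clinics |
| Clinic Services Form | No | Clinic total of HIV tests, not linked to participants' partners |

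For partner testing, J12 is the only direct measure collected alike in both arms. For disclosure there is a second measure, H4, but it is of limited use and may not be repeated.

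**2. How large could the bias be?** All values here are assumed, except the number retained. Suppose the package has no effect on testing and 50% of partners are tested in each arm. Let a0 and a1 be the proportions abstaining at follow-up in comparison and intervention clinics, and r the tested share among the extra abstainers in intervention clinics. The other abstainers are taken to have the 50% tested share.

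- Comparison, among those asked: 50%.
- Intervention, among those asked: [(1 − a0) × 0.5 − (a1 − a0) × r] / (1 − a1).
- Difference: (a1 − a0)(0.5 − r) / (1 − a1).

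The protocol expects at least 2520 patients retained at 12 months, or 2520/2 = 1260 per arm. With a0 = 10%, 1260 × 0.9 = 1134 are asked in the comparison arm.

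| a1 | Asked, intervention | r = 20% | r = 50% | r = 80% |
|---|---|---|---|---|
| 10% | 1134 | 0 | 0 | 0 |
| 15% | 1071 | +1.8 points | 0 | −1.8 |
| 20% | 1008 | +3.75 | 0 | −3.75 |
| 30% | 882 | +8.6 | 0 | −8.6 |

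For example, at a1 = 30% and r = 20%: (0.45 − 0.04)/0.70 = 58.6%, against 50%.

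**3. Would counting abstinent patients as successes solve it?** Take as the outcome having no untested recent partner, with abstinent patients meeting it. Assume half of partners untested, no testing effect, and abstinence (tested/untested partner) of 15%/25% in comparison and 15%/45% in intervention clinics.

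- Among those asked: 0.85/(0.85 + 0.75) = 53.1% v 0.85/(0.85 + 0.55) = 60.7%, a spurious 7.6 points.
- With abstinence as success: 1 − 0.5 × 0.75 = 62.5% v 1 − 0.5 × 0.55 = 72.5%, a spurious 10 points.

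The composite keeps everyone in the denominator but is further from a testing effect.

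**The case against.** The strongest reply is that the gap is narrower than it looks, and that what remains is an unstated denominator, which a protocol may leave to the analysis plan.

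- **Disclosure is asked outside the skip.** This stands for H4e and H4f. A reader might infer that they disappear at follow-up. The Data collection section does not list the dropped items, and H4 could be kept or reworded to a recent period. Appendix H is headed as the baseline questionnaire, although it has tick boxes for the later assessments, and no separate follow-up form is shown.
- **A test during an abstinent period is not wholly lost.** This stands in part. The Lay Counselor Record can capture it and is abstracted in the chart review. But it is an intervention-clinic form, so it cannot support a comparison of arms.
- **An outcome for everyone can be built from J3 and J12.** This is true as a matter of derivation. But counting abstinence as success does worse in the example above, and scoring abstinent patients as having no tested partner penalises abstaining. Either way the abstinence effect enters an outcome meant to measure testing. Whether an abstinent patient's spouse was tested stays unknown.
- **The bias need not favour the intervention.** This stands. A reader might infer that the skip flatters the package. Nothing in the protocol says which patients would stop having sex, and abstaining is only one example in a list of messages.
- **A recent-partner roster fits hypotheses about sex partners.** This is fair for the construct, but the roster's membership still depends on behaviour after baseline.

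**Conclusion.** The point holds in this limited form. At 6 and 12 months, J12-J15 and J18-J19 are asked only if J3 is not No. An analysis of those asked conditions on a behaviour the intervention can change. The weakness is greater for partner testing, where J12 has no equivalent collected alike in both arms, than for disclosure, where H4 may survive as a lifetime item.

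The size is not known. Under the assumptions above it is roughly ±2 to ±9 points when abstinence is 5 to 20 points higher in intervention clinics. It is zero if abstinence is equal between arms or unrelated to testing. These are illustrations, not estimates.

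A reader might also infer that the main result is at risk. It is not: the outcome used for the sample size is any unprotected sex in the past 3 months, and a No at J3 is a valid answer of none. The conclusion assumes that the follow-up form keeps the J3 skip, as the same-battery statement implies. The change is worth making, but the trial's powered comparison does not depend on it.

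**What to change.** At 6 and 12 months, ask J12-J15 and J18-J19 about the spouse or main partner whatever the answer to J3, and where feasible about the partners named at baseline. Move the skip for abstinent patients to the sex-act items from J24, and reword the 90-day introduction to match. The J7 definitions of spouse and main partner do not require recent sex, so the questions still make sense for an abstinent patient.

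Analyse testing and disclosure for those partners in all enrolled patients, in the arm to which their clinic was randomised. Do not count abstinence as success in either outcome; report it separately. State whether H4 is repeated at follow-up.

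The cost is a changed skip and a few more questions for abstinent patients in an interview of about one hour. Following baseline partners also means carrying the first name or nickname from J6 forward between visits, which is why that part is only where feasible.
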